### Data management

To ensure the standardization and security of research data, all study data will be entered into a secure, password-protected electronic database accessible only to authorized research personnel. Double data entry and periodic data verification will be conducted to ensure accuracy. Each participant will be assigned a unique identification code to maintain the confidentiality of personal information. In accordance with institutional data retention policies, all physical and electronic records will be archived for five years following the publication of results, after which they will be securely destroyed.

### Adverse events

Safety monitoring will be conducted continuously. Any adverse events reported by participants or observed by staff will be recorded, detailing their severity and potential relationship to the intervention. All adverse events and reasons for withdrawal will be documented in detail and reported to the Ethics Committee and the clinical trial registry, and will be analyzed in future studies.

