## Method and analysis

### Study design

The study is designed as a single-center, four-arm, parallel-group, superiority randomized controlled trial. A total of 148 participants will be recruited from the Chengdu Sport University. All therapeutic interventions and data collection will be conducted at the School of Sports Medicine and Health, Chengdu Sport University.

Potential participants will be targeting individuals who underwent unilateral TKA at least one year prior. Eligible candidates will be contacted by telephone for preliminary screening. Those meeting eligibility criteria will be invited for an in-person baseline assessment and receive a comprehensive explanation of the study procedures. Written informed consent will be obtained before enrollment. A screening log will be maintained to document eligibility and reasons for exclusion. Participants will be consecutively recruited until the required sample size (n = 148) is achieved. Participants will be randomly assigned in a 1:1:1:1 ratio to one of four groups: the Control group, the PNE group, the BFRT group, or the PNE combined with BFRT group.

The study has received approval from the Ethics Committee of the Chengdu Sport University (Committee Reference Number: CDSUEC2026- 177) and is registered with the Chinese Clinical Trial Registry (Registration Number: ChiCTR2600125544). The trial will be conducted in accordance with the Declaration of Helsinki. Any protocol amendments will be promptly submitted to the Ethics Committee and updated in the trial registry. Given the low-risk nature of the interventions, an independent data monitoring committee will not be established. However, all adverse events will be recorded and monitored throughout the trial. Any serious adverse events (SAEs) will be immediately reported to the Ethics Committee.

The study period will span from May 2026 to July 2029. Participant recruitment will occur between May 2026 and July 2027. Follow-up assessments will be completed by July 2029. The study protocol was developed in accordance with the SPIRIT 2025 Statement, as shown in Fig. 1. The timeline for participant enrollment, interventions, assessments, and follow-up visits is detailed in Table 1.

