#### The BFRT group

Participants in the BFRT group will additionally undergo a 12-week supervised BFRT program conducted twice weekly for a total of 24 sessions [28, 44]. Before the intervention, participants will complete three familiarization sessions separated by at least 48 h to standardize exercise technique and minimize learning effects [45]. The individualized Arterial Occlusion Pressure (AOP) will be determined using a Doppler ultrasound probe (DV-600; Marted, Brazil) in the supine position [44]. Detailed procedures for AOP measurement are provided in Supplementary Appendix 2. The training intensity will be anchored to the participant's 1-repetition maximum (1-RM) for leg press and knee extension exercises assessed using standard resistance equipment (Nakagym, São Paulo, Brazil). The 1-RM assessment protocol is detailed in Supplementary Appendix 3 [44, 46]. The intervention will follow a progressive overload model. The first week served as an adaptation phase, employing a training intensity of 20% 1-RM, completed in 4 sets of 15 repetitions each. Starting from Week 2, the training intensity was increased to 30% 1-RM, and from Week 5, the number of sets per training session was increased to 5. Inter-set rest intervals will be standardized at 1 min. During training, cuff pressure will be set at 70% of the individualized AOP, and the cuff will be inflated immediately before the first set and deflated after completion of the final set [44].

To maintain training load stability and ensure BFRT efficacy, both the 1-RM and AOP will be reassessed every 4 weeks to adjust training loads and cuff pressure based on updated values. Throughout the intervention, adverse events and participant discomfort will be continuously monitored.

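### Analysis of adverse events and withdrawal reasons is deferred to future studies; the trial should report harms by arm, using capture that does not depend on very unequal contact

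*Protocol article*

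**What the plan says.** The Adverse events section of the Protocol article sets the recording rule: "Any adverse events reported by participants or observed by staff will be recorded, detailing their severity and potential relationship to the intervention". Its last sentence covers both adverse events and reasons for withdrawal. They are to be documented and "reported to the Ethics Committee and the clinical trial registry, and will be analyzed in future studies".

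The Study design section adds that "all adverse events will be recorded and monitored throughout the trial", that serious events go to the Ethics Committee at once, and that "Given the low-risk nature of the interventions, an independent data monitoring committee will not be established". Table 1 shows adverse-event recording as one continuous row, not split by arm. The BFRT section carries a further statement of its own: "Throughout the intervention, adverse events and participant discomfort will be continuously monitored".

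The Statistical analysis section describes mixed models for the primary and secondary outcomes and applies intention-to-treat to the efficacy analyses. It mentions neither adverse events nor withdrawal reasons, and adverse events are not among the listed outcomes.

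**The concern.** The deferral is a stated rule, and nothing elsewhere in the article offsets it. If it is followed, the main report will say whether the combined arm did better on KOOS₄ but not how many participants in each arm were harmed or left because of harm. Three things make this matter here.

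- The decision to have no monitoring committee rests on the interventions being low-risk. The by-arm harms data from this trial are the obvious evidence on that premise in this population.
- The Discussion says that superiority of the combined arm would be strong support for using it in practice. That recommendation would rest on efficacy alone.
- Withdrawal reasons are deferred in the same sentence, although the primary analysis assumes data missing at random and the Discussion names dropout as a limitation. Withdrawals caused by adverse events bear directly on that assumption.

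Once harms are tabulated, a second issue appears. Events enter the record when participants report them or staff see them, and the arms differ greatly in how often participants and staff meet.

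**Working it through.** The article gives no figure for adverse events, so there is no stated number to reproduce. The check has three parts.

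**1. Does anything offset the deferral?** The Adverse events section sends the analysis to later studies. The Statistical analysis section confines itself to efficacy outcomes. Study design and Table 1 provide for recording and monitoring, and the Adverse events section for reporting to the Ethics Committee and the registry. Recording and reporting events is not the same as summarising them by arm in the trial's results, and no section commits to that.

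**2. Scheduled contacts after baseline.** Inputs:
- Control has no intervention sessions (The control group).
- PNE has 2 sessions, at weeks 0 and 6 (The PNE group).
- BFRT is a "12-week supervised BFRT program conducted twice weekly for a total of 24 sessions", preceded by 3 familiarization sessions (The BFRT group).
- The combined arm receives both under the same protocols (The combined intervention group).
- Every arm has four post-baseline assessments, at weeks 12, 24, 36 and 48 (Outcomes; Table 1).

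Total = intervention sessions + 4 visits. Up to week 12 = intervention sessions + 1 visit. After week 12 = 3 visits.

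| Arm | Total | Up to week 12 | After week 12 |
|---|---|---|---|
| Control | 0 + 4 = 4 | 0 + 1 = 1 | 3 |
| PNE | 2 + 4 = 6 | 2 + 1 = 3 | 3 |
| BFRT | 24 + 3 + 4 = 31 | 27 + 1 = 28 | 3 |
| Combined | 24 + 3 + 2 + 4 = 33 | 29 + 1 = 30 | 3 |

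The excess over Control is 31 − 4 = 27 in BFRT and 33 − 4 = 29 in the combined arm. All of it falls up to week 12 (28 − 1 = 27 and 30 − 1 = 29). Leaving out the familiarization sessions gives totals of 28 and 30. These are counts of scheduled sessions; a PNE session and a training session in the combined arm could fall on the same day.

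**3. What could unequal capture do?** The documents give no detection rates, so this part is illustration only. Take two arms of 37 with the same true risk p and detection probabilities d₁ and d₂. The observed risks are p·d₁ and p·d₂, and the observed risk ratio is d₂/d₁ although the true ratio is 1. With p = 30% assumed:

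| Assumed detection | Observed risks | Ratio | Fisher's exact p < 0.05 |
|---|---|---|---|
| 60% vs 80% | 18% vs 24% | 1.33 | 6% of trials |
| 50% vs 90% | 15% vs 27% | 1.8 | 17% |
| 30% vs 90% | 9% vs 27% | 3.0 | 43% |

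Over assumed true risks of 20% to 40%, the chance of a false signal across these pairs runs from 4% to 60%. The range is wide because it is driven entirely by the assumed detection rates.

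**The case against.** The best defence is that the data will exist. Every event is to be recorded with severity and relatedness in all arms throughout the trial, and reported to the Ethics Committee and the registry. An article also condenses, so how events are elicited, and what the safety table looks like, may be set out in the full protocol or an analysis plan.

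Much of this stands, and it rules out several stronger readings that a reader might infer:

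- *That events are collected only spontaneously.* The text describes no standard enquiry but does not exclude one.
- *That no valid between-arm harms result is possible.* A descriptive table by arm could be made from the planned records. Bias should be smaller for serious events, and scheduled contact is equal after week 12.
- *That a seven- or eight-fold contact ratio is a seven- or eight-fold difference in capture.* It is not. An event from the training period can still be reported at week 12 in any arm.
- *That Control participants meet staff only four times.* The Discussion plans regular communication to retain participants, without limiting it to any arm or giving its frequency. The 4 is a count of scheduled visits.
- *That small arms are the defect.* How large a risk is compatible with zero events in 37 participants is a matter of arm size and does not bear on this point.

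It is also fair to say that safety is not a stated objective, and that the Discussion discloses the unequal therapist contact, though only for interpreting treatment effects.

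None of this touches the deferral. A separate analysis plan would have to contradict the sentence, not merely fill a gap. If the sentence is only loosely worded, correcting it is easier still.

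**Conclusion.** The point holds in two parts. First, as written, this trial's report would contain no by-arm analysis of adverse events or withdrawal reasons. This rests on the article's own words and needs no assumption. Second, raw between-arm counts, mainly of mild events during familiarization and the 12 weeks of training, are open to ascertainment bias, because capture as described depends partly on contact and scheduled contacts are 4, 6, 31 and 33. The expected direction is towards more recorded events in the two arms with BFRT. The size cannot be computed from the document; the ratios of 1.33 to 3.0 above follow only from assumed detection rates. The change is worth making and should precede the accrual of outcome data, since non-comparable capture cannot be repaired afterwards.

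**What to change.** Replace the closing words of the Adverse events section, which send the analysis to later studies, with a commitment along these lines:

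- The main results of this trial will give, by arm, the number and proportion of participants (95% CI) with any adverse event, any serious adverse event, any intervention-related adverse event and any adverse event leading to withdrawal, together with withdrawal reasons.
- The between-arm comparison will use the same standard adverse-event question, asked in all four arms at the existing week 12, 24, 36 and 48 visits.
- Events noted at training sessions will be listed separately and not added to the counts being compared.

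A matching sentence belongs in the Statistical analysis section. The cost is one extra question on the visit form, one table, and a protocol amendment submitted and registered by the route that Study design already describes. It needs no extra visits and leaves the sample size and efficacy analysis unchanged.

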### Patient and public involvement

While participants will not be directly engaged in the study design, their preferences regarding treatment burden and pain management will be considered throughout all stages of the research. Study findings will be shared with participants upon conclusion.

## Discussion

KOA is the most common form of OA, accounting for approximately 85% of the total disease burden. Its typical clinical manifestations include joint pain, stiffness, and functional impairment, which compromise joint stability and, in severe cases, may lead to loss of mobility, posing a major public health challenge [1, 2, 56]. TKA is an effective treatment option for patients with moderate-to-severe KOA. However, 10–34% of patients report CPSP after primary TKA [57]. CPSP not only hinders postoperative recovery but may also lead to disability, diminish quality of life, and place a substantial burden on patients, families, and the healthcare system. Therefore, identifying effective interventions to alleviate pain and improve functional outcomes in patients with CPSP following TKA is of great clinical significance.

The development and progression of CPSP are influenced by multiple factors, among which psychological factors and chronic inflammatory responses are considered major contributors [58–62]. To avoid anticipated pain, patients often limit or avoid physical activity, a behavior that may ultimately lead to functional decline, muscle atrophy, and heightened pain sensitivity. Decreased muscle strength and the persistent accumulation of abnormal or elevated biomechanical loads may cause joint or tissue damage, further exacerbating pain and ultimately forming a vicious cycle of pain, fear, avoidance, functional loss, and renewed pain [63–66]. PNE, as a psychological intervention designed to reshape patients' perceptions of pain and coping strategies, positively influences pain experiences by explaining the biological and physiological mechanisms involved in pain. It has demonstrated small to moderate efficacy in chronic musculoskeletal pain [23, 67–69]. Among patients with persistent chronic pain one year after TKA, PNE has been shown to have clinical significance for pain relief, but its role in improving function remains relatively limited [28]. BFRT, a low-intensity exercise modality that applies external pressure to the proximal limb to partially restrict arterial blood flow and occlude venous return, has attracted significant interest for its exceptional efficacy in inducing muscle adaptation and analgesia. The pain-relieving mechanism is believed to be associated with metabolic stress–induced endogenous opioid release and inflammatory modulation [38, 70–72]. Although BFRT demonstrates promising clinical prospects in various chronic pain and postoperative rehabilitation, no study has yet systematically evaluated its efficacy in patients with CPSP following TKA. Given the potential complementary mechanisms between PNE and BFRT, it is reasonable to hypothesize that combining PNE with BFRT may produce synergistic effects in pain reduction and functional improvement, potentially offering superior clinical benefits for patients with CPSP following TKA.

To the best of our knowledge, this is the first study to compare the effects of PNE and BFRT in patients with persistent chronic pain one year after TKA and to assess whether combining both approaches yields superior clinical outcomes. Should the final results demonstrate that the combined group significantly outperforms either single intervention group, it would strongly support the clinical application of this integrated rehabilitation strategy. If effective, the combined intervention may provide an integrated non-pharmacological rehabilitation strategy targeting both psychological and physical contributors to CPSP following TKA. It is noteworthy that patients undergoing TKA typically experience a natural trend toward pain resolution within three months to one year post-surgery [73], which may interfere with the interpretation of short-term intervention efficacy. Therefore, this study specifically recruits individuals who continue to experience CPSP one year postoperatively, aiming to minimize the influence of natural recovery and improve the accuracy of treatment-effect evaluation.

However, this study still has several limitations. Firstly, the relatively long follow-up period may increase the risk of participant dropout, potentially affecting the representativeness and the statistical power of the final sample. To mitigate this issue, strategies such as regular communication, progress feedback, and incentive-based engagement will be implemented during the study to enhance participant compliance and ensure data completeness. Secondly, this study primarily focuses on validating clinical efficacy and does not delve into the potential molecular mechanisms underlying the synergistic effects of PNE and BFRT. This direction warrants further exploration in future research. Finally, the four groups differ in therapist contact and supervision, and no attention-matched comparator is included. Consequently, non-specific effects related to therapist attention, supervision, treatment expectations, and therapeutic interaction cannot be completely separated from the specific effects of the interventions. Although intervention exposure and protocol deviations will be documented, the findings should be interpreted as the effects of the respective intervention strategies as delivered. Future studies incorporating attention-matched comparators are warranted to better isolate specific intervention effects.

## Data Availability

Data are available in a public, open access repository. Data are available on reasonable request.
